## Abstract

**Background:**

The prevalence rates of childhood obesity are increasing. The current multidisciplinary treatments for (childhood) obesity are effective but only moderately and in the short term. A possible explanation for the onset and maintenance of childhood obesity is that it reflects a maladaptive mechanism for regulating high levels of stress and emotions. Therefore, the current RCT study aims to test the effectiveness of adding an emotion regulation training to care as usual (multidisciplinary obesity treatment) in young inpatients (10–14) involved in an obesity treatment program compared to care as usual alone.

The research model for this RCT study states that when high levels of stress are regulated in a maladaptive way, this can contribute to the development of obesity.

**Methods:**

The current study will recruit 140 youngsters (10–14 years) who are involved in an inpatient multidisciplinary obesity treatment (MOT) program. After giving consent to participate in the study, youngsters will be randomly assigned, during consecutive waves, to one of two conditions: care as usual (receiving MOT) or intervention (receiving MOT in addition to emotion regulation training). The training itself consists of 12 weekly sessions, followed by a booster session after 3 and 5 months. The participants will be tested pretraining, post-training, and at 6 months’ follow-up. We hypothesize that, compared to the control condition, youngsters in the intervention condition will (1) use more adaptive emotion regulation strategies and (2) report less emotional eating, both primary outcome measures. Moreover, on the level of secondary outcome measures, we hypothesize that youngsters in the intervention condition, compared with the control condition, will (3) report better sleep quality, (4) undergo improved weight loss and weight loss maintenance, and (5) experience better long-term (6-months) psychological well-being.

**Discussion:**

This study will add to both the scientific and clinical literature on the role of emotion regulation in the development and maintenance of different psychopathologies, as emotion regulation is a transdiagnostic factor.

**Trial registration:**

The RCT study protocol is registered at ISRCTN Registry, with study ID “ISRCTN 83822934.” Registered on 13 December 2017.

## Background

### Childhood obesity: growing prevalence, multiple consequences, and modest treatment success

Recent prevalence rates collected by the World Health Organization [150] revealed that, worldwide, 18% of the school-aged children and adolescents (5–19 years old) are diagnosed with overweight and 8% with obesity. These prevalence rates have tripled since 1975, demonstrating the growing problem of pediatric overweight and obesity [150]. This causes a great concern for both the individual and the community, as obesity has high medical and psychosocial consequences, both in the short term and long term [153].

The well-researched and currently golden standard treatment for childhood obesity is Multidisciplinary Obesity Treatment (MOT). The overall goal of the treatment is to improve the distorted balance between the energy intake and energy expenditure by changing the diet and increasing the physical activity [29, 106]. MOT incorporates cognitive behavioral therapy with active involvement of the parents to support behavior change and enhance the psychosocial well-being [29, 106]. Positive effects of MOT have already been found on weight (body mass index, BMI − 0.5 SD), physical fitness, and psychosocial well-being [104, 113]. However, the long-term effects of MOT are still limited, as weight-loss maintenance seems very hard to attain [4, 29, 96, 103, 151].

In sum, the high prevalence rates of childhood obesity; the medical, psychological, and economic consequences; and the poor long-term treatment effects emphasize the need to study in depth all mechanisms leading to childhood obesity. Herein, a psychological perspective recently has gained attention. An increasing number of studies point to “stress” as an important factor in the development and maintenance of childhood obesity [8, 74, 79, 110]. For example, families with an obese child experience more stress [102], and daily hassles seem to have a significant impact on children’s eating behavior [44, 110]. However, although the contributing role of stress in obesity is well studied, treatment options have not been developed in response. Therefore, the present study will bridge this gap by evaluating the role of treatment in an RCT study.

### Stress conceptualization

Stress occurs when a person perceives (goal-related) danger, attaches personal significance to the situation for his or her well-being, and the available coping resources of the person fail to deal with the situation [88]. Next to the cognitive and emotional component, stress also contains a physiological component [88]. The latter can be seen as a related but different indicator of a stress experience [143], reflecting the physiological arousal, which prepares the person to cope with the stressor by fighting or fleeing, and the restoration of homeostasis. Two main physiological stress systems have been identified [36]. The first stress system is the hypothalamic-pituitary-adrenal axis with cortisol as the end product. The second stress system is the autonomic nervous system with the catecholamines, adrenaline, and noradrenaline as end products, for which heart rate variability (HRV) is used as a noninvasive biomarker to indirectly measure cardiac parasympathetic and sympathetic activity [91].

When stress is successfully managed, the “emotional homeostasis” will return, and in the long run, the emotional stability will not be fundamentally affected (see Fig. 1: eustress). Adversely, when the stress is not successfully managed, enhanced arousal and negative affects occur like chronic experiences of tension, danger, frustration, or rejection (see Fig. 1: emotional distress) [37, 70, 86]. Emotional distress is associated with psychopathology [39, 83, 97], medical diseases [125, 127, 129], and obesity [8, 42, 58, 79, 101, 123].

**Fig. 1 Fig1:**
[figure not shown]
Emotion regulation as underlying mechanism

### A framework for the stress–obesity relationship

For a thorough understanding on how emotional distress may be associated with weight gain and obesity, three processes need to be considered (see Fig. 1). First, when stress is not successfully managed, chronic activation of the physiological stress tonus entails, which results in an elevated cortisol production. Chronic cortisol hypersecretion is directly associated with the accumulation of fat by stimulation of the fat cell growth and dysregulation of the lipolysis. Indirectly, the elevated cortisol level increases the appetite, calorie consumption, and consequently the adiposity [21, 36, 116]. Second, emotional distress triggers a low-grade inflammatory process, which occurs directly by elevating the cytokine production and indirectly by its association with less sleep, imbalanced diet, and less physical activity that subsequently induce inflammation [71, 89]. This inflammation process may stimulate other hypothalamic pathways, resulting in increased food intake and finally obesity by resistance to the appetite-reducing factors leptin and insulin [31, 32]. The third mechanism concerns emotional or stress-induced eating, defined as “overeating in response to emotions and stress” [8, 28, 48]. When experiencing stress, people aim to neutralize the stress-related arousal by eating, even in the absence of hunger, as this gives a warm and good feeling in the short term. Especially eating comfort food (e.g., highly palatable food which is rich in sugar and fat) is known as reinforcing [90]. Moreover, it initiates an automatic learning process [48, 90, 110], facilitating emotional eating as the preferred behavior when feeling emotionally distressed. This is observed in both normal weight and overweight adults and children [24, 107, 142]. As emotional eating can foster eating beyond the saturation point, it can lead to an increased calorie intake and to overweight or obesity over time [55, 84].

Importantly, the relationship between emotional distress and obesity is not unidirectional but a vicious cycle can be assumed: obesity itself will lead to further emotional imbalance (e.g., physical and psychological well-being), which is hypothesized to further induce (a) enhanced cortisol, (b) low-grade inflammation, and (c) emotional eating (see Fig. 1) [3, 28, 92, 119, 134, 146, 149]. Furthermore, excessive body fat directly maintains the low-grade inflammation that may lead to higher stress sensitivity and a maintained emotional imbalance, as inflammatory cytokines from excessive body fat can affect the brain and its stress-related neuro-circuitry, neuroendocrine activity, and neurotransmitters [34, 75].

The above-mentioned drastic processes, resulting from unsuccessfully regulated stress, highlight the question as to why some people seem able to regulate their stress, while others are unable to do so. Although it might be that some experience more stressors [102], it is also plausible that some are less capable of regulating stress-related emotions, leading to chronic stress experiences. This brings us to the hypothesis that emotion regulation is playing a crucial role in the vicious cycle of obesity (Fig. 1).

### Emotion regulation: the missing link?

Emotion regulation (ER) refers to the actions by which individuals try to exert an influence on the emotions they have, when and how they experience and communicate them [67]. These actions implicate the use of several ER competences which refer both to ER abilities (e.g., demonstrating compassion) and strategies (e.g., cognitive reappraisal). ER is recently found to affect different psychological problems, such as depression, anxiety, chronic pain, and ADHD [9, 73, 109, 124], and is now recognized as a transdiagnostic factor playing a role in the etiology and maintenance of different kinds of psychological problems [64]. Based on the long-term effects on affect, behavior, and psychopathology, Aldao and colleagues [5, 6, 68] suggest a classification in adaptive ER strategies and maladaptive ER strategies. Especially for obesity, studies have found that the association between stress and weight gain is stronger when more maladaptive ER strategies are used, whereas ER seems to mediate the stress-eating relationship [8, 48, 144]. Interesting, recent studies also emphasize the need to research adaptive ER strategies, as these are protective factors [27]. Commonly, in the literature, three adaptive ER strategies, “cognitive reappraisal,” “acceptance,” and “problem solving” have been researched and are found to be associated with less psychopathology (2009). Moreover, the adaptive ER abilities “acceptance,” “support yourself,” and the strategy “analyze and reappraise” are found to be trainable with positive effects in young adolescents [147, 148]. However, next to learning these ER competencies, also the sequence of applying them when feeling stressed is important [95, 111]. Therefore, Berking and Whitley [18] combined all these theoretical insights on ER competencies into a conceptual theory and training model on ER in adults, called Affect Regulation Training (ART). The ART model is in accordance with the recent literature on ER flexibility, referring to the importance of momentary flexibility in the use of different ER abilities and ER strategies across different stressful contexts taken into account the personal goals [7, 23]. Interesting, ART, both as a stand-alone intervention and on top of care as usual, is shown effective in clinical and nonclinical adult populations [15, 17, 18, 60]. Currently, our research group is evaluating the ER sequence, based on Berking and Whitley [18], in a prevention program for children and adolescents in schools [147], but it has not yet been evaluated in the context of emotional eating in a sample of obese children. However, given the evidence for the mediating role and the trainability of ER, we assume that an ER training will have good effects also for obese children. Therefore, in the preparation phase of the current RCT study, the feasibility of learning ER abilities and adaptive ER strategies in a population of obese youngsters has been investigated and well evaluated ([name], [name], [name], [name] & [name]: A Two-Hour Emotion Regulation Workshop in Early Adolescents with Obesity: A Feasibility Study, in preparation).

### Goals and hypotheses

As in the presence of stress, flexible and adaptive ER is a requisite to achieve eustress and avoid the detrimental pathways to weight (re)gain and obesity, an ER training may empower the current MOT and foster long-term weight loss maintenance (see Fig. 1). The present study will therefore examine the effectiveness of a newly developed 12-week ER group training (one training session of 2 hours per week) on top of the MOT by means of a randomized controlled trial (RCT) in an inpatient treatment center for childhood obesity. The addition of an ER training to the MOT compared with MOT “as usual” is hypothesized to result in 1) an improvement in ER competencies (assessed by means of self-report questionnaires, idiosyncratic measures, and validated with physiological parameters during a lab task) (=primary outcome); 2) less emotional eating behavior (assessed by means of self-report questionnaires and in a stress paradigm); 3) better sleep quality (assessed by means of self-report questionnaires); 4) improved weight-loss and weight-loss maintenance (in terms of adjusted BMI and waist circumference) with associated change in metabolic parameters; and 5) better long-term (6-month) psychological well-being (assessed by means of self– and parent report questionnaires). The protocol was registered at ISRCTN Registry with study ID: ISRCTN 83822934.

## Methods/Design

### Participants

Participants will be recruited in an inpatient treatment center for obesity in Belgium, *Het Zeepreventorium*, between March 2018 and September 2020. During consecutive waves, recruitment takes place at intake (T0; 4 months before starting the inpatient treatment) and both the youngsters and one of the parents should participate in the study. Inclusion criteria of the study are (1) 10–14 years old at the start of the inpatient treatment; (2) primary obesity, with minimum 60% overweight at intake in the treatment center according to the overweight index of Cole, Bellizzi, Flegal, and Dietz [38]; and (3) language proficiency, with mastery of the dominant language.

### Procedure

At recruitment (T0), the youngsters meeting the inclusion criteria and at least one of their parents will both receive detailed information from the researcher and the psychologists of the inpatient treatment center. After receiving this information on the study procedure orally and by letter; the youngsters and at least one of their parents will fill out an active informed consent. To obtain the target number of participants, *N* = 140 (power analysis, see below), a 2 ½ year recruitment period, March 2018 until September 2020, is necessary. After giving informed consent, participants are randomly assigned (see Randomization) to one of the two conditions: intervention condition or control condition. In the intervention condition, the ER training sessions will be given by trainers, who were also involved as clinical psychologists in the development of the ER training.

The Ethics Committee of the Ghent University Hospital approved the study design, procedure, and data collection. The national laws and the Helsinki Declaration of 1964 will be applied in all data collection procedures.

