### Study design

The study design concerns a two-arm randomized controlled trial, evaluating the effects of an emotion regulation training intervention versus a care-as-usual control group. Assessments in the two conditions are planned at four time points: after recruitment (T0), before the start of the intervention (T1), after the end of the intervention (T2), and at 6-months’ follow-up (T3). Primary outcome measures are emotion regulation and eating behavior, more specifically emotional eating. As secondary outcome measures, (1) weight change, (2) psychological well-being, and (3) sleep quality will be taken into account.

After giving informed consent (T0), participants and their parents will fill out questionnaires assessing the psychological well-being, ER capacities, and perceived stress of the child (parent- and self-report), which will be used for descriptive purposes or as covariates. Next, before the start of the intervention (T1), at the end of the intervention (T2), and at 6 months’ follow-up (T3), participants will fill out questionnaires on their psychological well-being, sleep quality, ER capacities, eating behavior, and perceived stress level, and they will participate in a stress paradigm. On top, at T1, the participants will also complete the Standard Progressive Matrices test to determine their overall cognitive ability. Parents of the participants will be asked again to fill out questionnaires on the psychological well-being and the eating behavior of their child at T2 and T3. Moreover, the participants in the intervention condition will be asked to fill out a diary three times a week on their stress level, affect, ER capacities, and emotional eating behavior between the ER training sessions. Filling out a diary enables a more momentary inspection on the relationship between the stress level, ER capacities, and emotional eating behavior in the naturalistic environment of the participants.

The eligibility, allocation, and assessments are illustrated in Figs. 2 and 3.

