### Randomization

Stratified randomization is a two-stage process, used to control for the influence of covariates (baseline characteristics), in the randomization process [135]. In the current RCT study, both sex and age are identified as potential and important covariates. Therefore, separate blocks for each combination of the covariates will be generated (e.g., girls 10–12, boys 10–12, girls 13–14, and boys 13–14).

Participants who give consent to participate the study will be assigned to one of the four blocks.

Afterward, simple randomization to one of two conditions (e.g., experimental vs. care as usual condition) will be applied within each block at the individual level using dice [82]. The dice is thrown by the same researcher in all consecutive waves. Based on our a priori power calculations that 140 participants have to be included, we will recruit participants until each of the blocks has 35 participants.

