#### Analytical plan

To solve the problems of noncompliance and missing outcomes, which are iterative complications in an RCT study, the intention-to-treat (ITT) principle will be used [69]. Multilevel analyses will be used to test the treatment effects, allowing handling of the missing and nested data from the two conditions (intervention versus control condition). More specifically, mixed models with fixed effects for condition (intervention versus control condition), time (immediately after intervention and 6 months’ follow-up), and their interaction, adjusted for baseline will be used.

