A first strength of the study is the use of a rigorous design, including a care-as-usual control group (MOT), randomization of the participants and six-month follow-up measurements to evaluate the effect of the EuREKA-training in an inpatient treatment for obesity [56]. A second strength is the use of different measurement methods (questionnaires, stress paradigm, and physiological measures) and informants (youngsters and parents) at all four data collection time points (T0, T1, T2, and T3). A third strength is the well-evaluated ART model and training, which has been the basis for the development of the EuREKA training that will be used in this study [16, 18]. Fourth, including homework in the EuREKA training is an advantage since it has the potential to increase the feeling of competence of the learned competencies in the training sessions [76].

This study also has some limitations. First, the control group is passive, and we will be unable to control for several aspects such as extra attention, rewards, and homework in the intervention group in comparison with the control group. Second, practical obstacles are expected. Therefore, a feasibility study preceding the RCT study in an inpatient treatment center for obesity was conducted, and practical difficulties concerning the organization, such as planning the extra therapy during school hours, were taken into account. However, new unforeseen obstacles cannot always be avoided. Second, no double-blind paradigm can be used, as the researchers will know who belong the EuREKA training intervention group. A consequence is a possible contamination in the instructions by the researchers and the participants of the intervention condition trying to perform better (Hawthorne effect) [78]. However, this lack is common in educational research trials [78].

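### As written, randomisation follows consent at T0 and does not wait for T1, so emotional eating, sleep and the stress paradigm get their baseline after allocation in a trial with unblinded researchers

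*Protocol article*

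**What the plan says.** Three places in the protocol article tie randomisation to consent:

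- Abstract, Methods: "After giving consent to participate in the study, youngsters will be randomly assigned, during consecutive waves, to one of two conditions".
- Procedure: "After giving informed consent, participants are randomly assigned (see Randomization) to one of the two conditions".
- Randomization: "Participants who give consent to participate the study will be assigned to one of the four blocks", after which dice decide the arm within each stratum. The same researcher throws them in every wave.

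Participants places consent in time: "recruitment takes place at intake (T0; 4 months before starting the inpatient treatment". Study design puts the next two assessments "before the start of the intervention (T1), at the end of the intervention (T2". At T0, children and parents report on well-being, emotion regulation and perceived stress, for description or as covariates. Eating behaviour, sleep quality and the stress paradigm enter the child's list at T1.

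The limitations in the Discussion state that "no double-blind paradigm can be used, as the researchers will know who belong the EuREKA training intervention group". They name two consequences: contaminated instructions from the researchers, and intervention children trying to perform better.

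The Analytical plan says "To solve the problems of noncompliance and missing outcomes, which are iterative complications in an RCT study, the intention-to-treat (ITT) principle will be used". Its mixed model has the post-training and 6-month times as outcomes and adjusts for baseline, without saying whether baseline means T0 or T1.

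**The concern.** A baseline covariate is safe when allocation cannot have influenced it. Measuring it before randomisation, or while everyone involved is still blind, guarantees that. Here the stated order does neither for the measures that begin at T1. The protocol itself names a route by which knowledge of the arm could reach the data, and nothing in the text keeps that route away from T1, which combines an instructed laboratory task with self-report. At T2 and T3 an unblinded trial has to accept the risk. At T1 it can be avoided.

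The second issue is loss between randomisation and T1. A child who is randomised and then leaves before T1 counts in the intention-to-treat population but has no baseline for these outcomes. The protocol describes drop-out as high and allows 10% for it.

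**Working it through.** **1. Order of events.** Consent is at T0, four months before inpatient treatment (Participants). Randomisation comes after consent (abstract, Procedure, Randomization). T1 comes after T0 and before training (Study design). No sentence places randomisation after T1. No sentence dates the dice throw or T1, and T1 is not placed relative to admission.

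**2. Which outcomes are affected.** Emotion regulation and well-being are measured at T0 and T1, so a T0 value exists for them. Child-reported emotional eating, sleep quality and the stress paradigm are first listed at T1, so T1 is their only possible baseline.

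**3. Bias from a shifted baseline.** Suppose knowledge of allocation moves the T1 score of the intervention arm by δ SD in the direction of benefit and leaves T2 and T3 unchanged. With T1–outcome correlation ρ, the baseline-adjusted effect has bias = −ρ × δ. All values of ρ and δ below are assumptions; the protocol gives none.

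| ρ | δ = 0 | δ = 0.1 | δ = 0.2 | δ = 0.3 |
|---|---|---|---|---|
| 0.3 | 0 | −0.03 | −0.06 | −0.09 |
| 0.5 | 0 | −0.05 | −0.10 | −0.15 |
| 0.7 | 0 | −0.07 | −0.14 | −0.21 |

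A shift in the opposite direction, or the same shift in the control arm, reverses the sign. A simulation with 63 per arm, a true effect of 0.50 SD and ρ = 0.5 gave a mean estimate of 0.402 for δ = 0.2 and 0.500 for δ = 0.

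**4. Bias from unequal early loss.** If leavers differ from stayers by k SD, the comparison of those who remain is off by k × (difference in loss between arms). With k = 0.5 and a 10-point difference (both assumed): 0.5 × 0.10 = 0.05 SD.

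**5. Drop-out allowance.** The plan's own figures first. Sample size gives 63 per arm for 80% power at .05, then 70 per arm with the 10% allowance. The target difference is 0.5 BMI points and no SD is given. Taking SD = 1 and a two-sided test (both assumed), n = 2 × (1.960 + 0.842)² / 0.5² = 62.8, so 63. Then 63 / 0.9 = 70. Both figures reproduce.

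The allowance is 7 per arm, or 14 of 140. If 5% leave before T1 (assumed), 140 × 0.05 = 7 children, half of it. If 10% leave, 140 × 0.10 = 14, all of it. If the planned 10% is lost later as well, then under the same SD = 1 assumption:

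| Loss before T1 (assumed) | Evaluable per arm | Power | Per arm needed to keep 63 |
|---|---|---|---|
| 0% | 70 × 0.90 = 63.0 | 80.1% | 70 |
| 5% | 70 × 0.95 × 0.90 = 59.9 | 78.1% | 74 |
| 10% | 70 × 0.90 × 0.90 = 56.7 | 75.9% | 78 |
| 20% | 70 × 0.80 × 0.90 = 50.4 | 70.9% | 88 |

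Randomising after T1 puts the first row into effect, because earlier losses then precede randomisation.

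**The case against.** The strongest reply is that the text gives an order and not a schedule. Every consented trial randomises after consent, and drawing lots in consecutive waves would fit a draw made later for a whole wave. The figures on allocation and assessments might settle it, and they are not shown. This stands against any claim about the length of the gap. A reader might infer that allocation precedes T1 by at least four months, or that T1 follows admission. Neither is stated: the four months run from T0 to the start of inpatient treatment. What remains is that three passages link randomisation to consent and none links it to T1.

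Three further points stand in part.

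- A reader might infer that every adjusted analysis uses a baseline taken after randomisation. The document does not support that, because emotion regulation and well-being also have T0 values and the model does not name its baseline.
- A reader might infer that children know their arm at T1. The Discussion says only that researchers will know, and does not say when.
- A reader might infer that the model contradicts the intention-to-treat statement. No rule excludes children without T1. The gap follows from the form of the model: an absent covariate is not handled in the way a missing outcome is. The remedy may sit in an analysis plan that is not shown.

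There may also be a practical reason to allocate early. Training runs in age-based groups of five, and the protocol reports difficulty in fitting the sessions around school hours. That affects the cost of the change and is met by the sealed-allocation option below.

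**Conclusion.** The point holds as a weakness in the order of steps that is cheap to remove. For child-reported emotional eating, sleep and the stress paradigm, the text as written places the baseline after randomisation, with researchers unblinded and contaminated instructions acknowledged. The result is a risk of bias and not a demonstrated bias: 0.03–0.21 SD over the assumed ranges for shift and correlation, and zero if T1 scores do not respond to allocation. Unequal early loss could add about 0.05 SD under the assumptions in the working. Losses before T1 weaken the intention-to-treat aim for these outcomes and draw on the 10% allowance. With 5–20% early loss on top of 10% later loss (assumed), power falls from 80% to between 78% and 71%. That power figure rests on SD = 1 for the weight index and is only a guide for the self-reported outcomes. For the same reason, expressing the bias as a share of a planned 0.5 SD effect would not be justified: the plan states 0.5 BMI points with no SD.

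**What to change.** For the remaining waves, randomise each wave once every child in it has completed T1. In the abstract, Procedure and Randomization, replace the wording that ties allocation to consent with, for example: *Randomisation takes place wave by wave, after all children in the wave have completed T1.* In the Analytical plan, name T1 as the baseline in the mixed model.

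If groups must be planned earlier, keep the allocation sealed from children, parents and T1 testers until T1 is complete. The researcher who throws the dice should then not run T1. Sealing closes the knowledge route, but children lost before T1 stay in the randomised set, so the first option is better where it is feasible.

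The cost is that the age-based groups of five are formed at shorter notice. Reaching 140 randomised children also takes more consents: with an assumed 10% loss before T1, 140 / 0.9 = 155.6, so 156. Record which waves used which order.
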